### Data Analysis

#### Overview

Primary data analyses will account for covariates that have been shown to be associated with cognitive change in MS—age, sex, disease duration, MS subtype (relapsing vs progressive subtypes combined), disease severity, personality variables, and cognitive reserve (education level plus scores on vocabulary test). After primary analyses are completed, analyses will be repeated stratifying by sex, age group, baseline cognitive impairment, and MS subtype. We have intentionally included participants with both existing cognitive impairment and no known cognitive impairment at enrollment. This will allow us to also conduct sensitivity analyses to explore whether people who show evidence of cognitive impairment at baseline show a more rapid decline on either laboratory or ambulatory cognitive assessments as has been identified in prior research [78,79].

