## Methods

### Study Design

The Optimizing Detection and Prediction of Cognitive Function in Multiple Sclerosis (CogDetect-MS) study applies an observational design that combines microlongitudinal (ie, frequent, repeated “burst” measures across 14 consecutive days) and longitudinal (ie, 1- and 2-year follow-up) data collection methods in a sample with MS. Participant recruitment and data collection are conducted across 3 sites: the University of Michigan (UM; lead site and data coordinating center) in Ann Arbor, Michigan; Wayne State University (WSU) in Detroit, Michigan; and the University of Washington (UW) in Seattle, Washington. Ambulatory data are managed by researchers at the Pennsylvania State University, who return scored and combined ambulatory datasets to UM.

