### Study Sample and Recruitment

The aim was to recruit 250 participants, with the expectation that 210 would also provide data at the final (2-year) follow-up. Participants were recruited through existing participant registries; electronic health record queries; institution-specific, participant-recruitment websites; clinic- and community-based recruitment; posting of flyers; and outreach to local partners, such as the local chapters of the National MS Society. Inclusion criteria (assessed by self-report) were (1) 18 years of age or older, (2) able to fluently converse and read in English, (3) MS diagnosis (confirmed via medical record review; all relapsing and progressive subtypes included), and (4) able to ambulate either independently or with the use of a cane or walker (or similar device) for at least 50% of the time at baseline; participants who lose ability to ambulate over the course of the study are retained, as this criteria only applies to initial enrollment. Exclusion criteria were (1) MS relapse within the past 30 days (may become eligible after 30 days; criteria used at T1, T2, and T3) and (2) inability to use study data collection tools (ie, ActiGraph wGT3X-BT [ActiGraph], smartphone app; volunteers “pass” this final exclusion criterion by independently completing a trial of the ambulatory assessment battery during the laboratory visit).

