### Participant Screening, Enrollment, and Data Collection Procedures

Volunteers underwent an initial prescreening by telephone to determine general inclusion or exclusion criteria and were fully screened at the T1 laboratory visit to establish study eligibility. MS diagnosis was either preconfirmed through medical record review or initially gathered by self-report and later confirmed through record review. Written informed consent procedures were either conducted remotely (via Zoom [Zoom Video Communications] or telephone, and a signature obtained via e-consent in REDCap [Research Electronic Data Capture; Vanderbilt University]) prior to the T1 laboratory visit or in person at the laboratory visit.

Participation in this study involves assessments at baseline (T1), 1-year follow-up (T2), and 2-year follow-up (T3). Each assessment period includes a ~2.5-hour laboratory visit immediately followed by a 14-day ambulatory monitoring period (measurement “burst”). At each laboratory visit, certified examiners administer cognitive and physical function test batteries and demonstrate the use of a study-specific smartphone (programmed with a data collection app) and an ActiGraph wGT3X-BT accelerometer for the collection of ambulatory data. A battery of web-based self-report surveys is also completed at each time point, either prior to (within 30 days of laboratory visit) or during the laboratory visit.

During each ambulatory monitoring period, participants continuously wear an ActiGraph wGT3X-BT to passively collect physical activity data. At 4 intervals throughout the day (wake, midday, and bedtime), participants complete a set of brief, valid, and reliable cognitive tests assessing processing speed and working memory [13] along with a battery of ecological momentary assessment (EMA; real-time self-report) measures of somatic symptoms, mood, functioning, behaviors, and context on the smartphone app. The wake-up and bedtime assessments are initiated by the participant when waking up (ie, waking and not necessarily getting out of bed) and going to bed (ie, “lights out” and not necessarily when getting into bed). The other 2 assessments are prompted by an audible alert on a quasi-random schedule determined by their usual waking time. At the end of each home monitoring period, participants return the ActiGraph wGT3X-BT and smartphone in a prepaid mailer to the laboratory for data download.

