### Examiner Certification Process

To ensure standard test protocol administration across study sites and time, a rigorous examiner certification process was established. To achieve initial certification to administer tests, research staff were required to read the study protocol and manual of procedures, read the NIHTB Administration Manual, watch all training videos, and pass quizzes at the end of each training video. Training videos were from the NIH Toolbox eLearning Course or were custom-made by the study investigators, who had expertise in motor testing ([name]) or neuropsychological test administration ([name], [name], and [name]). The videos provide detailed instructions on general best practices for test administration and how to administer each non-NIHTB test. After these initial training activities, research staff practiced the full laboratory-visit protocol with at least 5 nonparticipants (eg, fellow laboratory staff), video recording the final testing session. This video along with all accompanying case report forms and test materials were evaluated by 2 investigators—one with expertise in administering motor tests and one with expertise in administering neuropsychological tests. Together, the evaluators decided whether the examiner passed or failed the certification. Failure is defined as 2 or more minor errors or 1 or more major errors. A major error is defined as any error that indicates a lack of understanding of the proper standardized administration of any test or any scoring error that is large enough to change the interpretation of the data. Errors are reviewed with the examiner and their site principal investigator ([name], [name], or [name]). If the assessment is failed, the examiner practices at least 1 more time and submits a new certification video for review; this process can continue until the examiner passes certification. After initial certification, the examiner can begin testing study participants and is required to video record the first testing session with a person with MS; this video is also reviewed for consistency with study protocol, and feedback shared with the examiner. To ensure continued adherence to testing protocol, examiners record the laboratory visit for every 10th session, and this recording is reviewed by investigators as with the earlier certification videos. Consent for video recording is included in the study consent form.

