## Results

This research received funding on August 1, 2021, from the Eunice Kennedy Shriver National Institute of Child Health & Human Development (R01HD102337-01A1). Enrollment and T1 data collection occurred between May 12, 2022, and February 29, 2024. The study recruited 301 individuals with MS (UM: n=107, WSU: n=102, and UW: n=92); of these, 274 (UM: n=101, WSU: n=88, and UW: n=85) participated in T1 data collection. Longitudinal data collection will continue through March 2026. Data analysis has not yet started as of the time of this submission.

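### Study site is not among the stated covariates of a three-site observational cohort, which leaves the between-person long-term models of Aims 2 and 3 open to a probably small site bias

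*Protocol article*

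**What the plan says.** Study Design describes a study that is not randomised (the "study applies an observational design that combines microlongitudinal" and annual follow-up data) and states that "Participant recruitment and data collection are conducted across 3 sites". Study Sample and Recruitment lists routes that include "institution-specific, participant-recruitment websites; clinic- and community-based recruitment". The screening and data collection section adds: "At each laboratory visit, certified examiners administer cognitive and physical function test batteries". The Examiner Certification Process places each examiner under a site principal investigator and gives its purpose as "To ensure standard test protocol administration across study sites and time". Results reports that "274 (UM: n=101, WSU: n=88, and UW: n=85) participated in T1 data collection".

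The Data Analysis overview says "Primary data analyses will account for covariates that have been shown to be associated with cognitive change in MS" and lists "age, sex, disease duration, MS subtype (relapsing vs progressive subtypes combined), disease severity, personality variables, and cognitive reserve". Sample Size Analyses points to that list when it allows for up to 6 covariates beside 6 predictors. Site does not appear in the list, in the planned stratified repeats (sex, age group, baseline impairment, subtype), or in any model under Specific Aims 1 to 3. The multilevel models are not given a site level. The long-term models of Aims 2 and 3 regress the 1- and 2-year outcome on earlier ambulatory measures, adjusting for the outcome's baseline value.

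**The concern.** The predictors (activity, sleep, fatigue, pain, mood, stress, and in Aim 3 cognition) are observed, not assigned. Three centres in different cities, recruiting partly through their own channels, can differ in these predictors. They can also differ in the outcome, through case mix or through how staff give and score laboratory tests. If they differ in both, pooling them without a site term produces a predictor-outcome association that exists in no single site.

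Certification, re-review of sessions, audits and coordination meetings reduce differences in test administration. They do nothing about differences in who is recruited. The covariates were chosen for their known link to cognitive change, and a design variable such as site would not enter on that criterion.

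At stake is the reading of the long-term coefficients, which the article wants to use to identify targets for intervention. Site is known for every participant, so this source of bias can be removed.

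**Working it through.** **1. The plan's own figure.** Inputs from Sample Size Analyses: f² = 0.075, one-sided α = .01, 6 + 6 = 12 terms, 95% power, N = 214, critical t = 2.34. For one regression coefficient, the noncentrality is √(f²·N) and df = N − k − 1. With N = 214 and k = 12, df = 201, critical t = 2.345 and power = 0.9508. At N = 213 power is 0.9498, so 214 is reproduced.

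**2. Size of the bias.** The documents give no site differences, so the offsets below are assumptions. Site shares are 101/274, 88/274 and 85/274 (Results), and n = 210 is the expected final sample. Let predictor, baseline outcome and follow-up outcome carry the same standardised site offsets, with no association within sites. Let v be the between-site variance of the offsets and ρ the within-site correlation of baseline with follow-up, assumed to be 0.6 to 0.9.

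- Ignoring baseline: r = v/(1 + v).
- Correlation of baseline with follow-up: r₁₂ = (ρ + v)/(1 + v).
- Partial correlation given baseline: r_p = r·√[(1 − r₁₂)/(1 + r₁₂)] / √(1 − r²).
- False rejection rate: 1 − Φ(2.326 − r_p·√210), with √210 = 14.49.

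Worked example: UW alone differs by 0.5 SD, ρ = 0.6. v = (85/274)(189/274)(0.25) = 0.0535; r = 0.0508; r₁₂ = 0.6535/1.0535 = 0.620; r_p = 0.0246; 2.326 − 0.356 = 1.970; error = 2.4%.

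| Scenario | v | r, ignoring baseline | Error, ignoring baseline | r_p (ρ = 0.9 to 0.6) | Error given baseline |
|---|---|---|---|---|---|
| One site (UW), 0.3 SD | 0.019 | 0.019 | 2.0% | 0.004 to 0.009 | 1.2 to 1.4% |
| One site (UW), 0.5 SD | 0.053 | 0.051 | 5.6% | 0.011 to 0.025 | 1.5 to 2.4% |
| WSU and UW opposite, 0.3 SD | 0.057 | 0.054 | 6.1% | 0.012 to 0.026 | 1.6 to 2.6% |
| WSU and UW opposite, 0.5 SD | 0.158 | 0.136 | 36% | 0.029 to 0.063 | 2.9 to 7.9% |

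The choice of site matters little. A deviating UM gives at most 2.6%, and UM against WSU in opposite directions gives at most 8.8%.

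**3. What T1 does not remove.** The table assumes the same site offset at baseline and follow-up. A site difference in change, for example from drift in test administration, passes through the baseline adjustment. The documents give no basis for sizing it.

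**4. Cost of the site terms.** With k = 14, power at N = 214 is 0.9508 and the required N stays 214. At N = 210 power is 0.9468 with 12 terms and 0.9468 with 14. If site explains a share R² of the predictor's variance, f² becomes 0.075(1 − R²). For R² of 2%, 5% and 10%, power at 210 is 0.942, 0.935 and 0.921, and the required N is 218, 225 and 237.

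**The case against.** The strongest reply is that the list names substantive prognostic covariates and does not claim to be the whole model; a design variable such as site may sit in an analysis plan that is not shown. That is possible. But the list is stated rather than left open, and the sample size section relies on it, so an analyst who follows the text would fit no site term.

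Four points on reach and size stand:

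- A reader might infer from the correlations that ignore baseline that the error could reach 36%. The documents do not support this, because both long-term models adjust for baseline, which absorbs most of a stable offset. The listed covariates may absorb some case-mix difference as well.
- A reader might take all of Aims 2 and 3 to be affected. Site is constant within a person and cannot confound a purely within-person short-term association. The article does not say that predictors are person-mean centred, so this protection holds for the within-person part only.
- Examiner effects reach only the laboratory cognitive and motor tests. The phone tests are self-administered on an identical loaned device, activity and sleep come from an accelerometer, and the surveys are self-report.
- The certification scheme reduces examiner differences. It is not evidence that they exist, and no section reports a site difference.

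**Conclusion.** The omission is real and worth correcting, but minor. It concerns the between-person long-term models of Aims 2 and 3, chiefly those with laboratory outcomes. Under the assumed stable offsets of 0.3 to 0.5 SD, aligned on predictor and outcome, a nominal 1% one-sided test would reject about 1.2 to 2.5% of the time with one deviating site. With WSU and UW deviating in opposite directions it would reject about 1.6 to 8% of the time. The upper end needs the largest offsets, opposed sites and the weakest baseline correlation together. Three things remain unknown: the actual site differences, the baseline-to-follow-up correlation, and whether sites differ in change. The Aim 1 comparison is paired within person and is less exposed.

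**What to change.** Add study site as a fixed effect (two indicators) to the covariates in the Data Analysis overview, for the between-person long-term models of Aims 2 and 3. Three sites are too few for a well-estimated random effect. A site-by-time term in the models of laboratory test change is optional, as a sensitivity analysis.

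The cost is one phrase and 2 degrees of freedom, with no new data. Power is essentially unchanged unless site is strongly related to a predictor, which is also when the adjustment is most needed. Results states that analysis had not begun at submission; if that is still so, the term can be prespecified.

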### CogDetect-MS Study Measures: Laboratory Visit Measures

#### Self-Report Measures

The self-report survey battery includes surveys of demographics, clinical characteristics, and medical history (eg, medications and therapies) and a selection of valid and reliable self-report measures (Table 1 and Multimedia Appendix 1).

**Table 1 table1:** Validated self-report surveys administered in the Optimizing Detection and Prediction of Cognitive Function in Multiple Sclerosis (CogDetect-MS) study.

Domain	Measures
Sleep	PROMIS^a^ Sleep Disturbance Short Form 8b [36] STOP-Bang [37]
Fatigue	PROMIS Fatigue Short Form 8 V1.0 [38] Michigan Fatigability Index Short Forms
Pain	PROMIS Pain Intensity 3a [36] PROMIS Pain Interference 8a [39-41] painDETECT [42] American College of Rheumatology Fibromyalgia Diagnostic Criteria [43,44]
Depressed mood	PROMIS Depression 8b [45]
Stress	Perceived Stress Scale [46]
Social functioning	Neuro-QoL Ability to Participate in Social Roles and Activities Short Form 8 [47,48]
Cognitive function	PROMIS Cognitive Abilities Short Form 8 [49] Compensatory Cognitive Strategies Scale [50]
Physical functioning	Neuro-QoL Upper Extremity Function-8 [47] Neuro-QoL Lower Extremity Function-8 [47] Patient Determined Disease Steps [51]
Falls	1-Month Falls History Falls Efficacy Scale [52] Fear of Falling Avoidance Behavior Questionnaire [53] Concern and Fear of Falling Evaluation [54,55]
Substance use	Tobacco, Alcohol, Prescription Medications, and Other Substances Tool [56-58]
Comorbidities	Comorbidity Questionnaire [59]
Personality^b^	Ten-Item Personality Inventory [60]
Demographic and clinical variables	Demographic and clinical characteristics survey Pet ownership survey [61]

^a^PROMIS: Patient Reported Outcomes Measurement Information System.

^b^Evaluated at T1 visit only.

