##### Long Term

Ambulatory measures of predictor and outcome variables will be aggregated within a time period for baseline and 1- and 2-year follow-up periods. Laboratory-based measures of cognitive functioning will also be examined. MLMs will be used to test whether ambulatory measures of physical activity, sleep, fatigue, pain, mood, and stress predict changes in objective or subjective measures of cognitive functioning (ambulatory and laboratory-based measures) 1 or 2 years later. The change will be modeled within an analysis of covariance framework, where T2/T3 values for an outcome of interest are modeled controlling for T1 values of the said outcome. In contrast to specific aim 1, where the primary interest is on comparing the performance of the ambulatory tests to standard clinic-based cognitive tests, the primary interest of specific aim 2 is in understanding what factors contribute to variation or changes in cognitive function and in identifying probable targets for cognitive rehabilitation regardless of the measure used to identify such associations; therefore, no direct comparisons between measurement types will be made.

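### The primary covariate list omits comorbidity, which is collected at every wave, so other illness is an unadjusted potential common cause in the long-term Aim 2 and 3 models

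*Protocol article*

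**What the plan says.** The Data Analysis Overview gives both the rule for choosing covariates and the result. The rule is: "Primary data analyses will account for covariates that have been shown to be associated with cognitive change in MS". The result is "age, sex, disease duration, MS subtype (relapsing vs progressive subtypes combined), disease severity, personality variables, and cognitive reserve", with cognitive reserve defined by education and a vocabulary score. Sample Size Analyses refers to this list for the Aim 2 and 3 models. The analyses are then repeated by sex, age group, baseline cognitive impairment and MS subtype. Comorbidity is in neither place.

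Table 1 lists a comorbidity questionnaire under Comorbidities and STOP-Bang under Sleep. On timing, the data collection section states: "A battery of web-based self-report surveys is also completed at each time point". The only exception marked in Table 1 is personality ("Evaluated at T1 visit only").

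Study Sample and Recruitment has two exclusions: an MS relapse in the past 30 days and inability to use the data collection tools. Participants must be 18 or older and able to walk, with or without a device, at least half of the time.

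The long-term Aim 2 analysis is set out as follows: "MLMs will be used to test whether ambulatory measures of physical activity, sleep, fatigue, pain, mood, and stress predict changes in objective or subjective". The outcomes that this sentence goes on to name are cognitive scores one or two years later, and the T1 value of the outcome is adjusted for. Part of the stated interest lies "in identifying probable targets for cognitive rehabilitation regardless of the measure used to identify such associations".

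**The concern.** A confounder is related to both exposure and outcome. The article's rule considers only the relation to cognitive change, not the relation to activity, sleep, fatigue, pain, mood and stress. Illness other than MS could plausibly affect several of these as well as cognition and physical function. Disease severity, disease duration and subtype describe MS and are not measures of other illness.

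The long-term models use values aggregated over each burst, so the comparison is largely between people. Strengths and Limitations credits the within-person design with accounting for third variables, but the long-term models do not gain that protection. If comorbidity is a common cause, part of an apparent link between, say, inactivity and later cognition would belong to other illness, and a rehabilitation target could be chosen on it. Long-term Aim 3 is open to the same problem, because comorbidity could affect both cognition and later physical or social function.

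**Working it through.** **1. The plan's own figure.** Sample Size Analyses uses a linear regression with 6 covariates and 6 predictors (k = 12), f² = 0.075, α = .01 one-sided and 95% power, giving N = 214.

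- Noncentrality: √(f²·N) = √(0.075 × 214) = 4.006.
- Degrees of freedom: 214 − 12 − 1 = 201. Critical t = 2.345 (the article prints 2.34).
- Power = 0.951, so N = 214 is reproduced.
- The partial correlation implied by f² is √(0.075/1.075) = 0.264.

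**2. Assumptions.** The documents give no correlations for comorbidity. Let c be its correlation with an exposure and b its correlation with T1-adjusted cognition, net of the other terms. The exposure has no true effect. N = 210, the number expected at two years. The spurious correlation is r = (partial correlation of comorbidity with the exposure) × b. The rejection probability comes from the same noncentral t, with f² = r²/(1 − r²) and k = 12.

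**3. Comorbidity tied to one factor only.** With c = 0.3 and b = 0.2 to 0.4, r = 0.06 to 0.12, which is 23 to 45% of 0.264. False positives are 4.4 to 20% two-sided and 7.2 to 28% one-sided. Simulation on the one-sided test gave 6.9% at (c, b) = (0.3, 0.2) and 14.8% at (0.3, 0.3). Both fell to about 1% once comorbidity was in the model.

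**4. The planned joint model.** The Aim 2 power calculation enters six predictors together. If comorbidity correlates c with all six and they intercorrelate ρ, each partly stands in for it. Given the other five:

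- partial covariance with one predictor = c(1 − ρ)/(1 + 4ρ);
- residual variance of the predictor = 1 − 5ρ²/(1 + 4ρ);
- residual variance of comorbidity = 1 − 5c²/(1 + 4ρ).

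For ρ = 0.2: 0.3 × 0.8/1.8 = 0.1333; variances 0.8889 and 0.75; partial correlation 0.1333/√0.6667 = 0.163. For ρ = 0.5: 0.05/√(0.5833 × 0.85) = 0.071.

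| ρ | partial correlation | r for b = 0.2 to 0.4 | two-sided .01 | one-sided .01 |
|---|---|---|---|---|
| 0.2 | 0.163 | 0.033 to 0.065 | 1.88 to 5.12% | 3.17 to 8.31% |
| 0.3 | 0.120 | 0.024 to 0.048 | 1.46 to 3.02% | 2.38 to 5.11% |
| 0.4 | 0.092 | 0.018 to 0.037 | 1.26 to 2.12% | 1.96 to 3.60% |
| 0.5 | 0.071 | 0.014 to 0.028 | 1.16 to 1.65% | 1.69 to 2.76% |

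The one-sided column matches the test in the sample size section, taking the bias to run in the hypothesised direction. The table is for Aim 2. The article says Aim 3 models have fewer predictors, so the dilution there would be weaker; this was not computed separately.

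**5. Cost of one more covariate.** With k = 13 the required N stays 214. Power is 0.951 at N = 214 and 0.947 at N = 210, the same as with k = 12, provided the partial f² is unchanged.

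**The case against.** The list follows its stated rule, and the documents do not show that comorbidity meets it. The article is also condensed, so a sensitivity analysis using comorbidity may exist in the full protocol or SAP. This stands in part: it cannot be said that no analysis anywhere uses the questionnaire. But the article gives a specific list for the primary analyses without marking it as examples, and that choice can be judged.

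The walking requirement keeps out some severe physical illness, and age is already a covariate. Adjustment for the T1 outcome and MS severity removes part of any confounding. All of this stands, and it points to the lower end of the ranges.

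Three stronger readings are tempting and are not supported:

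- A reader might infer a false-positive rate of 4 to 20% per factor. That holds only if comorbidity is tied to one factor alone, and b = 0.4 exceeds the 0.264 partial correlation that the study expects for mood.
- A reader might infer that STOP-Bang should also be a primary covariate. The article lists it only under Sleep. Entering it in every model would adjust one sleep measure for another and could remove part of the sleep association under study.
- A reader might infer that the study will report causes. The article speaks of prediction, associations and probable targets, and sends the findings on to trials. Its language about contributing factors and targets is still enough for confounding to matter.

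The point does not extend to the short-term models. A stable comorbidity drops out of within-person effects if predictors are centred at the person mean, which the article does not specify.

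**Conclusion.** The point holds for the long-term Aim 2 and 3 models: a potential common cause is measured at each wave but absent from the stated primary covariates. This is a weakness in the choice of covariates, not a contradiction in the document. The omission is documented; the size of the bias is not. Under the joint-model assumptions for Aim 2, the excess is modest: about 1 to 5% false positives per factor two-sided, or 2 to 8% one-sided, instead of 1%. It is larger only if comorbidity is concentrated on a single factor. The case for changing the list rests on the low cost and on the use to be made of the results, more than on a large demonstrated bias.

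**What to change.** Add the T1 comorbidity score to the covariates of the long-term Aim 2 and 3 models. First check the questionnaire's items, which the article does not show, and leave out any that duplicate an exposure such as pain or depressed mood. Report the long-term results with and without the score. Name STOP-Bang as a sensitivity analysis for the sleep results only, again shown both ways.

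The cost is one covariate from data already being collected, with negligible loss of precision and no extra participants. Some over-adjustment is possible, and the paired results would show it. The article states that data analysis had not started at submission; if that is still so, the change can be prespecified.

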Effects sizes from a prior study of perceived cognitive functioning in daily life in MS [73-75] informed sample size estimation for the second and third aims, which examines factors that predict later cognitive decline or that are predicted by cognitive changes. We calculated the sample size needed to test the aims in a linear regression framework [76], which is a relatively conservative estimate, given that the repeated measures design imparts greater measurement reliability and therefore greater power [77]. We based our estimates on models that included up to 6 covariates (see list of covariates below) and 6 predictor variables of interest (eg, sleep quality, physical activity, pain, fatigue, mood, and stress) in predicting any given cognitive variable. The sample size for these models was expected to provide a conservative estimate for power required for the third aim (which had fewer predictors in each model). Critical α (*P*) value was set at .01. Our analyses indicated that a sample size of 214 will have 95% power (critical *t*=2.34, 1-sided significance test) to detect an association between cognitive functioning, and the variable expected to show the weakest association with cognition: mood (effect size *f*^2^=0.075).

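### Subgroup differences are approached only by repeating analyses within strata, with no test of whether results differ; if impairment is set from the outcome's own T1 score, regression to the mean adds a bias

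*Protocol article*

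**What the plan says.** The Overview under Data Analysis lists the covariates for the primary analyses and then states that "analyses will be repeated stratifying by sex, age group, baseline cognitive impairment, and MS subtype". It goes on to say that enrolling people with and without impairment permits a sensitivity check, whose purpose is given as: "explore whether people who show evidence of cognitive impairment at baseline show a more rapid decline on either laboratory or ambulatory cognitive assessments". No model is given for that second question. The article names no interaction term or between-stratum comparison, and it does not say which measure or cut-off defines baseline impairment.

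Sample Size Analyses treats the whole cohort only. For aims 2 and 3 it assumes "models that included up to 6 covariates (see list of covariates below) and 6 predictor variables of interest", states that "Critical α (*P*) value was set at .01", and concludes that "a sample size of 214 will have 95% power (critical *t*=2.34, 1-sided significance test") for the weakest predictor, "mood (effect size *f*^2^=0.075"). Study Sample and Recruitment plans 250 participants, "with the expectation that 210 would also provide data at the final (2-year) follow-up".

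Two treatments of the T1 score matter here. Aim 1 sorts participants by change from T1 in SD units (Sample Size Analyses and Specific Aim 1), with no conditioning on T1 stated. The long-term models of Specific Aims 2 and 3 adjust for the T1 value of the outcome.

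**The concern.** A set of stratified repeats invites the reader to compare strata: an association present in relapsing but not progressive MS, or in unimpaired but not impaired participants. Separate fits do not test that difference. When strata are unequal, a significant result in the larger and a non-significant one in the smaller is what equal effects with unequal power commonly produce. The comparison would be made over four factors, several predictors and several cognitive outcomes, so such contrasts would be frequent.

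The impairment factor may carry a further problem. People selected for a low T1 score on a test tend to score higher on that test at T2 without any true change. The article expects impaired people to decline faster, so this artefact would pull against the expected result and could hide or reverse it.

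**Working it through.** **1. The plan's own figure.** Power for one regression coefficient comes from the noncentral t distribution with noncentrality √(f²·N) and N − 13 degrees of freedom (12 terms plus intercept). With f²=0.075, one-sided alpha .01 and N=214, the critical t is 2.345 and power is 95.1%. The stated figure reproduces. At the expected 210, power is 94.7% one-sided and 91.3% two-sided.

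**2. The same effect inside strata of 210.** The article gives no stratum sizes, so the shares are assumptions. Let p₁ and p₂ be power in the smaller and larger stratum when the true effect is identical in both.
- Only the larger is significant: p₂(1 − p₁).
- Exactly one is significant: p₁(1 − p₂) + p₂(1 − p₁).

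| Split | Sides | p₁ | p₂ | Only larger | Exactly one |
|---|---|---|---|---|---|
| 32 / 178 (15%) | 1 | 18.8% | 90.3% | 73% | 75% |
| 32 / 178 | 2 | 12.3% | 85.1% | 75% | 76% |
| 52 / 158 (25%) | 1 | 33.7% | 86.1% | 57% | 62% |
| 52 / 158 | 2 | 24.7% | 79.6% | 60% | 65% |
| 63 / 147 (30%) | 1 | 41.6% | 83.2% | 49% | 56% |
| 63 / 147 | 2 | 31.8% | 75.9% | 52% | 59% |
| 105 / 105 (50%) | 1 | 67.0% | 67.0% | n/a | 44% |
| 105 / 105 | 2 | 57.1% | 57.1% | n/a | 49% |

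For example, at 15% one-sided: 0.903 × (1 − 0.188) = 0.73.

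**3. What an interaction test would deliver.** Suppose the slopes differ by as much as the whole mood effect. The noncentrality is √(0.075 × 210) × √(s(1 − s)), where s is the smaller share. That is 3.97 × 0.50 = 1.98 for an equal split and 3.97 × 0.433 = 1.72 for 25/75. Two-sided power is 27% and 19% at alpha .01, and 51% and 40% at alpha .05. The test holds false contrasts at alpha, but the study is not sized to detect effect modification.

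**4. Regression to the mean, if impairment is a cut-off on the outcome's own T1 score.** With no true change and retest reliability r, mean change in those below cut-off c is (1 − r)·φ(c)/Φ(c). The ratio φ(c)/Φ(c) is 1.53 at c = −1 and 1.94 at c = −1.5. Cut-offs and reliabilities are assumptions.

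| r | Apparent gain, c = −1 | Apparent gain, c = −1.5 |
|---|---|---|
| 0.75 | 0.38 SD | 0.48 SD |
| 0.85 | 0.23 SD | 0.29 SD |
| 0.95 | 0.08 SD | 0.10 SD |

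Aim 1 places the lower limit of meaningful decline at 0.5 SD, so the upper end of this range is not small. Specific Aim 3 assumes the ambulatory measures are the more reliable. On that assumption, with each test's own T1 score setting impairment, the artefact would be larger on the clinic tests.

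**5. Does it matter which test sets impairment in aim 1?** A simulation with no true change set impairment by a clinic score below −1 SD. Assumed reliabilities were 0.7–0.9 for clinic tests and 0.95 for ambulatory tests, with a correlation of 0.7 between true scores. The ambulatory test then showed the greater decline category in 34–38% of the impaired and 24–26% of the unimpaired. Using the clinic outcome test to define the group is enough to create a subgroup contrast.

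**The case against.** The strongest reply is that the article never says subgroup differences will be concluded from which stratum reaches significance. A reader might infer that rule, but the text says only that analyses will be repeated, and stratum estimates shown as description are legitimate. The full protocol or analysis plan, not shown, may add interaction terms. The first part stands, and no such inference rule should be attributed to the authors. The second does not remove the point: stratified repetition is the one subgroup method the article states, and it cannot answer a between-group question.

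A reader might also take the faster-decline question to be answered by the stratified repeats. It is a separate sensitivity analysis with no stated model. Specific Aim 1 already plans mixed models of change over time, where a time-by-impairment term would fit, so it is not ruled out.

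A third tempting reading is that the plan builds in regression to the mean. The article does not support that. Impairment could mean known clinical status or a rule over several tests. The aims 2 and 3 long-term models adjust for T1 and are much less exposed.

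Finally, the power figures use the weakest expected predictor and assumed shares, and the article calls its regression framework conservative. The short-term multilevel models are not described by these figures. Actual T1 enrolment was 274. At the planned retention of 210/250, that is about 230 at two years, and repeating step 2 with 230 gives 47–77% for only the larger stratum. The conclusion does not change.

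**Conclusion.** The point holds in a limited form. Repeating the analyses within strata cannot show that results differ between strata. At the plan's own effect size and alpha, identical effects would leave only the larger stratum significant about 49–75% of the time if the smaller holds 15–30% of 210. With equal halves, exactly one stratum would be significant 44–49% of the time. Each range spans one- and two-sided testing; the shares are assumed.

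The regression-to-the-mean point is conditional on impairment being set from a T1 score that is also the outcome. Its size depends on the assumed cut-off and reliability: 0.38–0.48 SD at 0.75, 0.08–0.10 SD at 0.95. It bears on the aim 1 raw-change categories and the decline-rate comparison.

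These are secondary analyses and the primary conclusions stand. The change is still worth making: Results states that analysis had not begun at submission.

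**What to change.** - In the full-sample models, add factor-by-predictor interactions for sex, age (kept continuous), baseline impairment and MS subtype. For the faster-decline question, add a time-by-impairment interaction.
- Report the interaction estimates with confidence intervals and label them exploratory. Keep stratum estimates as descriptive.
- For the aim 1 change categories and the decline-rate comparison, define baseline impairment once, the same for ambulatory and clinic outcomes, from a measure not used as the outcome. A definition that changes with the outcome would put different people in the impaired group on the two sides of the aim 1 comparison. If no separate measure is available, report the likely size of the regression-to-the-mean bias in a sensitivity analysis.

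The cost is wording and model specification; no new data are needed. The main downside is low power: 19–27% at two-sided .01 for a slope difference as large as the whole mood effect. A non-significant interaction must therefore not be read as evidence that subgroups are alike. Setting aside a separate measure for impairment also means it cannot serve as an outcome in those two analyses.
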